#### Body composition and blood pressure

We measure body composition and waist circumference (cm) at baseline and at 3 months of follow-up. Height (cm) is self-reported. Weight is measured to the nearest 0.1 kg. Waist circumference is measured two fingers above the umbilicus to the nearest cm using a non-stretchable Seca 201 circumference measuring tape.

Body composition, including body weight (kg), fat percentage, and skeletal muscle percentage is measured using the body composition monitor OMRON BF 511. By bioelectrical impedance, sending electrical currents from the hands via handheld electrodes to the feet via the scale’s surface electrodes, both the upper and lower body is accounted for in the assessment. An earlier model (OMRON BF 306) has been validated against the criterion method dual-energy X-ray absorptiometry (DEXA) [11].

Blood pressure and pulse is measured with the automatic blood pressure meter OMRON M7 after at least 5 min of rest. We use the upper right arm for measurement, and the participants are instructed to avoid talking or crossing their legs during the procedure.

#### Physical activity measurement

To assess physical activity and sedentary behavior objectively, we use the 3-axial accelerometer ActiGraph wGT3x-BT (www.actigraphcorp.com). The ActiGraph is widely used to capture and record continuous, high resolution physical activity and sleep/wake information. It has been reported to assess energy expenditure due to physical activity, as well as time spent in sedentary behavior, light, moderate and vigorous activity levels, with high accuracy [12, 13]. The ActiGraph is given to the participants at the baseline and at the follow-up meeting. It measures at the frequency of 80 Hz, and is worn at the wrist for 24-h a day during 7 days at baseline and at 3-month follow-up. Participants are also given a log-book to record non-wear time, for example when showering, swimming and bathing. The ActiGraph and the log-book is sent back to the researchers in a prepaid envelope.

#### Questionnaires

*Participant characteristics* are collected with questions on civil status, education, income, use of medications for hypertension, diabetes or hyperlipidemia, estimated number of days on sick leave last year and tobacco use.

*Diabetes risk* is assessed using FINDRISC (Finnish Diabetes Risk Score), a validated prediction tool to identify participants undiagnosed, or at risk of developing diabetes type 2. FINDRISC takes age, body mass index (BMI, kg/m^2^), waist circumference, physical activity, intake of vegetables, fruit and berries, medical treatment of hypertension, history of hyperglycemia and family history of diabetes into account [14].

*Sleep quality and restoration from sleep* is assessed with a short version of the validated Karolinska Sleep Questionnaire [15]. Participants also report habitual sleep as bed time (lights out), rise time and time falling asleep after lights out (subjective sleep latency). Thereby, subjective total sleep can be assessed as the time difference between bed time and rise time, minus sleep latency.

*Dietary intake* is measured using a validated 85 item semi-quantitative food frequency questionnaire (FFQ) [16]. The participants are asked how often they consume different food items, including alcohol, previous months. Response categories varies from seldom/never to three or more times per day. Additionally, five diet questions and two questions about drinking habits developed by the Swedish Board for Health and Social Welfare for use in clinical practice are included [17].

*Eating patterns* are assessed with 21 questions in Three Factor Eating Questionnaire (TFEQ-R21) [18], a widely used and for different populations validated questionnaire. The TFEQ-R21 encompasses three eating behaviors including cognitive restrained eating, emotional eating, and uncontrolled eating.

*Physical activity and inactivity* is assessed with two questions developed for clinical practice, assessing whether or not the participant reaches the guidelines of the World Health Organization for maintaining general health, i.e. ≥150 min of moderate-to-vigorous physical activity per week or ≥ 75 min of vigorous-intensity physical activity per week. Additionally, two questions about sitting time are included. We also ask if the participant has been exercising during the past week. Participants who report to having exercised are asked about the type of activity performed (strength training at the gym, aerobics, swimming/water aerobics, cycling or other) and frequency and duration of performing that activity.

*Health Related Quality of Life*, is assessed with RAND-36, a questionnaire with 36 questions covering eight different dimensions which can be compiled into the two domains: physical component summary scale and mental component summary scale [19].

*Purpose in Life,* i.e. the extent to which a person engages in activities that are personally valued, is measured with a Swedish translation of the 6-item Life Engagement Test [20].

*Perceived stress levels* is assessed using the 14-item Perceived Stress Scale (PSS-14) [21].

*Social support for a healthy lifestyle* (diet, physical activity and less stress) from family, friends and co-workers is assessed with a 6-item questionnaire.

*Stage-of-change, motivation to make lifestyle changes* in terms of diet, physical activity, sleeping habits, stress, alcohol and tobacco is assessed. The response options for these question are in accordance with Prochaskas’ transtheoretical model of behavior change using the five phases of pre-contemplation, contemplation, preparation, action, and maintenance to assess participants’ readiness to change now, within a month, within 6 months, not now, or not at all [22].

#### Sample size and power considerations

The purpose with Health Integrator is to personalize the lifestyle intervention to the particular need of the participant. To estimate the sample size needed to detect a significant difference within the Health Integrator Intervention study, we chose a change in general health score on the RAND 36-Item Health Survey, which includes both physical and mental health, as the primary outcome.

The intervention was planned to include 63 subjects in each group, providing 80% power at the 5% significance level given a two-sided significance level of 5%, to detect a difference in general health score on the RAND 36-Item Health Survey of eight points (55 vs. 63 points) given a standard deviation of 16 [23]. To allow for drop-outs and the fact that the lifestyle intervention is personalized and may focus on different areas of health, we aimed to recruit 300 participants in total.

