### Aim

The aim of this paper is to describe the study design and methodology of the Health Integrator Intervention. We aim to evaluate if a digital platform accessible via a smartphone-app offering lifestyle intervention, with and without additional health coach guidance, can be used to make lifestyle changes and improve health related quality of life (primary outcome) in gainfully employed persons. Secondary outcomes include improving levels of blood pressure, body composition, blood lipids, HbA1c and other health related lifestyle factors.

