### Statistical analyses

Descriptive statistics will be produced to describe participant characteristics at baseline and follow-up. Results will be presented by control and intervention groups. Baseline characteristics will be produced to assess the success of the randomization in balancing characteristics. Differences between groups will be assessed using Student’s t-test and chi-square test for continuous and categorical variables, respectively.

Longitudinal data will be analyzed using both generalized estimating equations (GEE) and Mixed Models with a robust covariance structure to assess the effect of both time and the intervention itself on the study outcomes. Any unbalanced baseline characteristics will be controlled for in models. Interactions will be tested for in the models and intention to treat analysis will be performed to account for effects of cross-over and drop-out. Sensitivity analysis to account for missing data will also be done and to further study if the effect of the intervention differs based on participant characteristics.

Finally, we will also analyze how the app is perceived and used. At 3-month follow-up, the intervention group will receive a 16-item questionnaire evaluating the usability and satisfaction with the Health Integrator application. From the Health Integrator system, we will also be able to get descriptive statistics on number of log-ins, fulfilled goals per participant and which lifestyle interventions or services that were the most chosen ones among the participants in the intervention groups.

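### The primary outcome is a change in general health score, but the 63 per group rests on score levels and an unlabelled SD of 16, so 80% power for an unadjusted change comparison is not assured

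*Protocol article*

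**What the plan says.** The Aim section gives the primary outcome only in general terms: "improve health related quality of life (primary outcome) in gainfully employed persons". The section on sample size and power makes it specific: "we chose a change in general health score on the RAND 36-Item Health Survey, which includes both physical and mental health, as the primary outcome".

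Its next paragraph gives the calculation. On group size it says "The intervention was planned to include 63 subjects in each group". Its power claim reads "providing 80% power at the 5% significance level", and the test is two-sided. The target is worded "to detect a difference in general health score on the RAND 36-Item Health Survey of eight points (55 vs. 63 points) given a standard deviation", and the value given for that deviation is 16, with a literature citation. The text does not say whether 55 and 63 are follow-up means in two arms, or whether 16 describes the spread of scores or of within-person changes. It gives no correlation between baseline and follow-up.

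The Statistical analyses section plans GEE and mixed models "to assess the effect of both time and the intervention itself on the study outcomes". It controls for baseline characteristics that turn out to be unbalanced. It does not say whether the baseline general health score is a covariate, one of the repeated outcomes, or neither.

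**The concern.** The declared outcome is a change, but the calculation is written as a comparison of two levels. The variability of a change differs from that of a single score unless the correlation between the two measurements happens to be 0.5. A reader who takes 16 as the SD of the score, which is the natural reading beside 55 and 63, cannot tell what power the trial has for the outcome it names.

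The analysis could remove the problem, because including the baseline score protects precision whatever the correlation. The article makes baseline adjustment depend on observed imbalance, so that protection is not planned. What is at stake is whether the quoted 80% applies to the primary comparison, and whether the trial uses a baseline measurement it already collects from every participant.

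**Working it through.** **Inputs from the sample-size section:** difference 8 points, SD 16, two-sided 5%, 63 per group, 80% power.

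**Assumed, because not stated:** correlation r between baseline and 3-month score, shown from 0.2 to 0.7; equal SDs at the two visits.

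**Step 1: reproduce the stated figure.** n per group = 2 × (1.960 + 0.842)² × 16² / 8² = 2 × 7.85 × 4 = 62.8, so 63. Power at 63 = Φ(8 / (16 × √(2/63)) − 1.960) = Φ(2.806 − 1.960) = 80.1%. The exact t-test gives 79.5%. The stated 63 is a plain two-sample comparison with SD 16, and its arithmetic is right.

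**Step 2: does the target effect differ between level and change?** No. Randomisation makes the expected baseline means equal, so an 8-point difference between arms at 3 months is also an 8-point difference in mean change. Only the SD can differ.

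**Step 3: if 16 is the SD of the score.**
- Unadjusted change: SD = 16 × √(2(1 − r)).
- 3-month score with baseline score in the model: SD = 16 × √(1 − r²).

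Power at 63 per group and n per group for 80%, by the normal formula of Step 1:

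| r | SD, change | Power, change | n for 80%, change | SD, adjusted | Power, adjusted |
|---|---|---|---|---|---|
| 0.2 | 20.2 | 60% | 101 | 15.7 | 82% |
| 0.3 | 18.9 | 66% | 88 | 15.3 | 84% |
| 0.4 | 17.5 | 73% | 76 | 14.7 | 87% |
| 0.5 | 16.0 | 80% | 63 | 13.9 | 90% |
| 0.6 | 14.3 | 88% | 51 | 12.8 | 94% |
| 0.7 | 12.4 | 95% | 38 | 11.4 | 98% |

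The adjusted analysis is never less precise than the change score, because 2(1 − r) − (1 − r²) = (1 − r)², which is never negative. It is never less precise than the level comparison, because 1 − r² is at most 1.

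**Step 4: if 16 is the SD of change.** The unadjusted change comparison has the stated 80% at 63 per group. The score SD is then 16 / √(2(1 − r)), and the adjusted SD is 16 × √((1 + r)/2), which is at most 16. Adjustment keeps power at about 80% or above under this reading too.

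**Step 5: the numbers recruited.** The Abstract reports 209 participants, or 209 / 3 = 69.7 per arm. With no drop-out, and 16 as the score SD, an unadjusted change comparison reaches 80% only if 62.8 × 2(1 − r) ≤ 69.7, that is, r of at least about 0.44. Ten per cent drop-out gives 69.7 × 0.9 = 62.7 per arm, about the planned 63.

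**The case against.** The strongest objection is that nothing has been shown to be wrong. The arithmetic reproduces, and the 8-point effect is the same for a level and a change. The SD of 16 comes from a cited source that is not at hand and may already be an SD of change. A shortfall needs three things together: 16 is a score SD, r is below 0.5, and the analysis leaves out baseline. The article establishes none of the first two and leaves the third open, and above r = 0.5 the stated power is conservative. All of this stands, so the table above is a sensitivity range and not a demonstrated loss.

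A reader might infer that the stated power belongs to a different endpoint, or that the longitudinal models necessarily estimate a difference in change. The document does not support either. Level and change share the same units and the same expected between-arm difference. The analysis section does not specify a time-by-arm contrast with baseline as a repeated outcome.

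It can also be said that a condensed article may leave the correlation and the model form to a fuller document. Their absence alone is therefore no finding. But the article itself prints both the outcome and the power inputs, in adjacent paragraphs, and they do not match as written. It also states its own rule for baseline adjustment, and that rule is conditional.

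Finally, the planned target of 300, or 100 per group, left a margin above 3 × 63 = 189. That margin was also meant to cover drop-out and the spread of intervention areas, and with 209 recruited little of it remains.

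**Conclusion.** The point holds in a limited form. The article defines the primary outcome as a change and supports its sample size with score levels and an unlabelled SD, so 80% power for an unadjusted change comparison is not assured. If 16 is the SD of the score and the SDs are equal at both visits, power at 63 per group is about 60% at r = 0.2, 80% at r = 0.5 and 95% at r = 0.7. The values of r are assumptions. If 16 is the SD of change, 80% stands.

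This does not show that the trial is underpowered or that the calculation is wrong. It shows that the stated power depends on a quantity the article does not give, and that the planned analysis does not commit to the adjustment that would remove the dependence.

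**What to change.** State one primary comparison in both sections: the general health score at 3 months between arms, with the baseline general health score always in the model, whether or not it is balanced. In the GEE or mixed model, enter the baseline score as a covariate or constrain the baseline means to be equal across arms. With 63 analysed per group, about 80% is then a lower bound at any r.

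This does not abandon the declared outcome. With the baseline score as a covariate, the estimated arm difference is the same whether the dependent variable is the 3-month score or the change from baseline.

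If the unadjusted change score is kept, either state that 16 is an SD of change, or give the SD of change and the assumed correlation and restate the power in place of the flat 80%.

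The cost is one sentence in the sample-size section and matching wording in the analysis section. No new data or participants are needed, because all participants answer the quality-of-life questionnaire at baseline. The trial is described as ongoing, so the statement should be dated and made before outcomes are compared between arms. Under the unadjusted option, the restated power may be less favourable.

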### Statistical analyses

Descriptive statistics will be produced to describe participant characteristics at baseline and follow-up. Results will be presented by control and intervention groups. Baseline characteristics will be produced to assess the success of the randomization in balancing characteristics. Differences between groups will be assessed using Student’s t-test and chi-square test for continuous and categorical variables, respectively.

Longitudinal data will be analyzed using both generalized estimating equations (GEE) and Mixed Models with a robust covariance structure to assess the effect of both time and the intervention itself on the study outcomes. Any unbalanced baseline characteristics will be controlled for in models. Interactions will be tested for in the models and intention to treat analysis will be performed to account for effects of cross-over and drop-out. Sensitivity analysis to account for missing data will also be done and to further study if the effect of the intervention differs based on participant characteristics.

Finally, we will also analyze how the app is perceived and used. At 3-month follow-up, the intervention group will receive a 16-item questionnaire evaluating the usability and satisfaction with the Health Integrator application. From the Health Integrator system, we will also be able to get descriptive statistics on number of log-ins, fulfilled goals per participant and which lifestyle interventions or services that were the most chosen ones among the participants in the intervention groups.

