### Participants and recruitment

Four companies are participating in the Health Integrator Intervention study. Two companies with white-collar office employees, including personnel at an insurance company (Länsförsäkringar Alliance) and administrative personnel of Sweden’s largest pharmaceutical retailer (Apoteket AB). We also recruited blue collar employees, i.e. bus drivers, from two companies in Stockholm; at the largest bus transport group in the Nordic countries (Nobina) and at Europe’s largest transport provider (Arriva).

Study participants were recruited in two different ways according to the wishes of each company. The office of human relations at the two companies with white-collar employees sent an inquiry email about the study to their employees. Those who were interested in participating in the study responded to the first email and research personnel then received the email addresses. Bus drivers, whose email addresses are unknown to the employer, were continuously recruited by study personnel on site at the bus garages and asked in person to provide their private email addresses if they are interested in participation. Employees from all four companies that were interested in the study, were thereafter emailed information about the study and a link to access the web-based baseline questionnaire.

Eligible participants were required to give their informed consent for participation in the study in connection with the web-based questionnaire. After an introductory screen displaying information about the study, participants had to consent to participate in order to continue to the questionnaire. At completion of the questionnaire, the respondent was provided with a link to the Health Integrator system.

In the Health Integrator system, each user created an individual user account with personal log in details and responded to a health profile that included 38 questions on physical activity, diet, sleeping habits, stress, alcohol habits, and tobacco use (smoking and oral moist tobacco). The participant also scheduled a time for the baseline meeting with the health coach. The results from the health profile were not visible in the system at this point.

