### Randomization and blinding

Once the participant had responded to the baseline questionnaire and scheduled a baseline meeting, they were randomized to one of the three arms using a random allocation list generated with STATA Version 14.0. We randomized by company and in blocks of 6 by gender.

The participant was randomized to 1 of 3 groups: 1) intervention using Health Integrator and a monthly telephone session with the health coach during the 3 months of follow-up (in total two sessions per participant) or 2) intervention using Health Integrator without extra health coach sessions or 3) control group which is not given any lifestyle advise during the intervention period. Subjects in the control group receive access to Health Integrator after 3 months when the active intervention is finished.

Due to the nature of the study, participants are informed about their allocation by study personnel at baseline assessments.

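### Covariates are to be chosen by observed baseline imbalance; company, gender and the use of the baseline score should be fixed in advance, or power may be lost and standard errors may be conservative

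*Protocol article*

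**What the plan says.** All places are in the protocol article.

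- **Randomization and blinding:** "We randomized by company and in blocks of 6 by gender". Under Participants and recruitment, "Four companies are participating in the Health Integrator Intervention study": two with office staff and two with bus drivers. Four companies by two genders gives up to eight strata.
- **Statistical analyses, first paragraph:** "Baseline characteristics will be produced to assess the success of the randomization in balancing characteristics". The next sentence is "Differences between groups will be assessed using Student’s t-test and chi-square test for continuous and categorical variables, respectively".
- **Statistical analyses, second paragraph:** "Longitudinal data will be analyzed using both generalized estimating equations (GEE) and Mixed Models with a robust covariance structure", and then the covariate rule, "Any unbalanced baseline characteristics will be controlled for in models". No criterion for imbalance is given. Company, gender and the baseline score are not named as covariates.
- **Sample size and power considerations:** for the primary outcome, "we chose a change in general health score on the RAND 36-Item Health Survey".

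**The concern.** Under sound randomisation, baseline differences between arms arise by chance. A difference between arms does not show that a variable predicts the outcome, and a strong predictor that happens to be balanced still brings precision when it is in the model. A rule that adjusts for whatever looks uneven therefore selects on the wrong property and leaves the final model unknown until the baseline tables have been read.

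The rule also works against the design. Company and gender were used to build the allocation lists, so they will be close to balanced and the rule will tend not to select them. A stratified design calls for them in the analysis, and here company also separates office staff from bus drivers.

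Precision is at stake. The trial recruited 209 of the 300 it aimed for, and prespecified adjustment is a cheap way to recover some information.

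**Working it through.** **1. The plan's own figure.** Inputs from Sample size and power considerations: difference 8, SD 16, two-sided 5%, 80% power.

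n = 2(1.960 + 0.842)² × 16² / 8² = 62.8, so 63 per group. The planned figure reproduces (power 0.801 by the normal approximation, 0.795 by the non-central t).

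**2. Baseline adjustment against an unadjusted change score.** Inputs: 209 recruited (Abstract), SD 16 and 8 points (sample-size section). Assumed: 20% loss and the baseline-follow-up correlation r. Completers per arm = 209 × 0.80 / 3 = 55.7. Power is from the non-central t.

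- SD of change = 16√(2(1 − r))
- SD after baseline adjustment = 16√(1 − r²)

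| r | SD, change | Power, change | SD, adjusted | Power, adjusted | Gain (points) |
|---|---|---|---|---|---|
| 0.3 | 18.9 | 60% | 15.3 | 78% | 18 |
| 0.5 | 16.0 | 74% | 13.9 | 86% | 11 |
| 0.6 | 14.3 | 83% | 12.8 | 91% | 7 |
| 0.7 | 12.4 | 92% | 11.4 | 96% | 3 |

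At r = 0.8 the two are almost the same (98.5% and 99.2%).

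**3. Leaving out the strata.** Let balanced strata explain a share R² of the outcome variance (assumed), with neither strata nor baseline in the model. The model standard error is then too large by a factor 1/√(1 − R²), and the actual size of a 5% test is 2(1 − Φ(1.96/√(1 − R²))).

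| R² | SE too large by | Actual size |
|---|---|---|
| 0.02 | 1% | 4.8% |
| 0.05 | 3% | 4.4% |
| 0.10 | 5% | 3.9% |
| 0.20 | 12% | 2.8% |

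**4. Simulation of the rule.** Settings: 189 participants in three arms, eight strata, blocks of 6, 6,000 runs per setting, one intervention-control contrast at one follow-up, follow-up score as the response. The conditional rule is taken here as adding the baseline score only if it differs at p < 0.05. The three settings of r / R² are 0.5/0.05, 0.6/0.10 and 0.7/0.10.

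| Analysis | Power | Type I error |
|---|---|---|
| Baseline only if p < 0.05, no strata | 0.819, 0.816, 0.827 | 0.041, 0.034, 0.028 |
| Baseline always, no strata | 0.894, 0.934, 0.969 | 0.048, 0.049, 0.047 |
| Baseline and strata always | 0.898, 0.937, 0.972 | 0.050, 0.051, 0.050 |

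At 0.6/0.10 under no effect, the conditional rule's mean model standard error is 2.82 against an empirical 2.63. With baseline always in the model and strata omitted, the two are 2.28 and 2.27. Most of the gain comes from the baseline score; the strata add little once it is present.

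**5. How often chance triggers the rule.** If imbalance means p < 0.05 in a single two-group comparison of m independent characteristics, the chance of at least one flag is 1 − 0.95^m: 40%, 64% and 79% for m = 10, 20 and 30. Both m and independence are assumptions.

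**The case against.** **An analysis plan not shown may list the stratification factors.** It may, and their absence from a journal article would not by itself be a fault. The point rests on what the article does state, which is a selection rule driven by the observed data.

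**The baseline score is already used.** A reader might infer that it enters only if it happens to differ between arms. The documents do not support that: the primary outcome is a change, and the planned models are longitudinal with a time effect, so baseline enters within the change or as a repeated response. The simulated conditional rule in step 4 is therefore an unfavourable reading and not the stated plan. A longitudinal model with baseline means constrained equal would lose almost nothing against baseline adjustment, but the article does not say that this constraint will be used.

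**Wrong standard errors.** A reader might fear false positives. The error shown is conservative only. It nearly vanishes once baseline is modelled, and stratum effects that are constant over time cancel from a change score. The planned robust covariance does not repair the omission of strata, but neither does that omission inflate type I error.

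**Selection by significance test is inferred.** This stands. The sentence on t-tests and chi-square tests follows the one on baseline balance, but the paragraph also covers follow-up and nothing ties those tests expressly to covariate choice. If they are not the criterion, the rule has none.

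**The rule looks at baseline data, not outcomes.** True, so it need not favour a particular treatment effect. It still leaves the model open until the data are inspected.

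**The SD of 16.** A reader might also infer that the sample size is wrong because the outcome is a change ("55 vs. 63 points) given a standard deviation of 16"). Whether 16 describes scores or changes depends on a cited source that is not at hand, and the two coincide at r = 0.5. The 63 per group reproduces, so no fault is claimed there.

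**Conclusion.** The point holds in a limited form. The article fixes a poor rule: covariates follow observed imbalance, so the model depends on chance, and the two factors used in the randomisation will tend to be left out. The consequence is a possible loss of precision, not a threat to validity.

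Against an unadjusted change score, the gain from prespecified baseline adjustment falls from about 18 points of power at r = 0.3 to about 3 at r = 0.7. It would be close to nil if the longitudinal model already constrains baseline means to be equal. The conservatism from omitted strata lies between negligible and a 5% test run at 2.8%, and the larger values need strata that explain 20% of variance with no baseline in the model. The values of r, R² and the 20% loss are all assumptions. The change should be made because it is cheap and removes an open choice from the primary model.

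**What to change.** Replace the sentence on unbalanced characteristics in Statistical analyses with:

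> All outcome models (3 and 6 months) include company and gender as prespecified covariates and use the baseline value of the outcome, either as a covariate with follow-up scores as the responses, or as a repeated response with baseline means constrained equal across arms, not both. Baseline tables are descriptive, and no covariate is added to the primary model because of observed imbalance.

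One of the two ways of using the baseline value should be chosen before the outcome data are analysed. The wording fits the planned GEE and mixed models, covers the 6-month visit and avoids using baseline twice. It costs about five degrees of freedom (three for company, one for gender, one for baseline) and needs no new data. Models with further covariates can still be reported as sensitivity analyses.
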